#### *Documentation of security parameters for routine*

A value outside the normal range or reference in a routine safety assessment, such as laboratory tests, vital signs, ECG, can mean an adverse finding. If the investigator finds that the abnormality has a major relevance, it must also register it in Adverse Event case report form. If the findings contribute to a clinical diagnosis (eg., Hepatitis, in the case of elevated liver enzymes), then this diagnosis should be recorded as an adverse event.

An abnormality should be considered an important clinical relevance if:

represent a serious adverse event, or led to premature discontinuation of the study, or required a therapeutic measure.

With respect to laboratory safety parameters, the investigator must classify each value outside the normal range at:

1. Abnormal but of secondary importance.
2. Abnormal and important relevance (seriously, leading to discontinuation, required a therapeutic measure) should be made to their record in the clinical record.
3. Invalid value, must be specified the reason for this trial.

#### *Documentation of adverse reactions expected*

The following selected adverse reactions (= causality adverse events with "probable" with the study drug Miltefosine) will not be recorded in the Adverse Event report form, but separate modules will be documented in medical records:

Vomiting: documentation of intensity (according to the scale CTCAE)

Diarrhea: documentation of intensity (according to the scale CTCAE)

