## 2. OBJECTIVES

The objective of this trial is to assess if therapeutic activity and safety of oral miltefosine patients with CL caused by *L. braziliensis* in an endemic area of Bahia state is similar or superior to the standard treatment (meglumine antimoniate – Glucantime®).

Primary endpoint:

- Rate of final cures (6 month after treatment)

Secondary endpoints:

- Rate of initial cure (2 month after treatment)
- Incidence and severity of adverse events

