A The term "life threatening" in the definition of "serious" refers to an event in which the patient is at risk of death at the time of the event, does not refer to an event that hypothetically might have caused the death would be more serious.

B clinically important conditions that may not result in death, be life-threatening or require hospitalization may be considered when SAE, based on appropriate clinical trial, may involve risk to the patient or require intervention to prevent one of the outcomes listed in the above definition .

Note: The term "severe" is often used to describe the intensity (severity) of an event (as in mild pain, moderate or severe), the event itself may be of relatively minor clinical significance (such as severe headache). Not the same as "serious", which is based on the outcome of event / patient or action criteria usually associated with events that pose a risk to the patient's life or vital function. Seriousness (not severity) serves as a guide for defining regulatory reporting obligations.

*Procedures in case of adverse events*

The investigator should ask the patient at each visit if he / she had any medical problem or not unusual.

All adverse events that occur during the study treatment should be documented, regardless of the assumption of a causal relationship in respective page of the report form (CRF). All symptoms / complaints that have occurred in the last 14 days before the first exposure to study treatment should be documented in "Complaints at Baseline" medical records.

The documentation of adverse events including start and end date, severity, according to the CTCAE criteria, and seriousness. The investigator should also assess the likelihood of a causal relation of adverse event to study medication as probable, not assessable, or unlikely. The information provided in the investigator's brochure can give support to this evaluation.

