| - CBC                                                    |       | x               |       | x     | x      | x      | x                       |                                  | x                                |                                   |                                   |                                   |
| - Biochemistry                                           |       | x               |       | x     | x      | x      | x                       |                                  | x                                |                                   |                                   |                                   |
| - Urine type 1                                           |       | x               |       |       |        |        | x                       |                                  | x                                |                                   |                                   |                                   |
| - ECG (control patients)                                 |       | x               |       |       |        |        | x                       |                                  |                                  |                                   |                                   |                                   |
| Vital signs                                              |       | x               | x     | x     | x      | x      | x                       |                                  | x                                | x                                 | x                                 | x                                 |

a Within the 14 days before the 1st dose (except for parasitological examination of lesions, which will be valid within the last 4 weeks)

b It should be evaluated fully when treatment is discontinued. The reason (s) for discontinuation is (are) documented (s). This applies also to patients who withdrew from the study due to any reason.

c Evaluation of selection performed in the first half of the menstrual cycle (<10 days of the cycle) in the case of a negative pregnancy test before randomization, the treatment can be initiated without waiting period.

Evaluation of selection performed in the second half of the menstrual cycle (> 10 days) pregnancy test followed by a waiting period of two weeks, during which they should be used adequate contraception. After the waiting period should be performed a confirmatory test of pregnancy, before randomization.  

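### Vomiting and diarrhoea are recorded differently by arm and by an unblinded causality call, so the adverse-event endpoint draws on unequal records

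*Protocol*

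**What the plan says.** Section 2 of the protocol names "Incidence and severity of adverse events" as a secondary endpoint and makes safety relative to antimony part of the objective.

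Section 3.4 holds two recording rules. Under Procedures in case of adverse events, the general rule reads "All adverse events that occur during the study treatment should be documented, regardless of the assumption of a causal relationship", on the relevant page of the report form. The items named there are start and end date, CTCAE severity and seriousness, plus a causality rating of probable, not assessable or unlikely.

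Under Documentation of adverse reactions expected comes an exception for selected reactions, defined as "causality adverse events with 'probable' with the study drug Miltefosine". These "will not be recorded in the Adverse Event report form, but separate modules will be documented in medical records". The two reactions are vomiting and diarrhoea, and the item listed for each is CTCAE intensity. Antimony is not mentioned.

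The Emergency measures text in section 3.3.3 names vomiting and diarrhoea as the known reactions to miltefosine. Section 3.1 describes an open trial, and section 3.2 plans 60 miltefosine and 30 antimony patients.

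**The concern.** Only a patient who received miltefosine can meet the condition for the exception. The general rule makes documentation independent of causality; the exception makes the place and content of the record depend on it. The person who makes the causality call knows the treatment.

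The events concerned are the ones the protocol itself expects from the test drug. If the endpoint were tabulated from the adverse-event form, these events would drop out of one arm only. If it were tabulated from both sources, the two arms would still be described with different items. A later analysis can merge data sets, but it cannot supply items that were never collected.

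**Working it through.** The protocol states no adverse-event rate, so there is no figure of its own to reproduce beyond the allocation: 90 × 2/3 = 60 and 90 × 1/3 = 30, as section 3.2 says. The main check is a reading of the two rules against each other.

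| Vomiting or diarrhoea in | Causality call | Where recorded | Items listed |
|---|---|---|---|
| miltefosine arm | probable | separate module | CTCAE intensity |
| miltefosine arm | not assessable or unlikely | general adverse-event record | dates, severity, seriousness, causality |
| antimony arm | any | general adverse-event record | dates, severity, seriousness, causality |

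Two consequences follow from the protocol's own definitions.

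- The exception has no carve-out for serious events. Vomiting that leads to hospitalisation meets the definition of a serious adverse event in section 3.4. If judged probable, it goes to a module for which seriousness is not listed.
- Section 3.2.3 defines dose-limiting toxicity as CTCAE grade 3 or 4 confirmed by re-assessment within a week. The modules list no dates from which that interval could be checked.

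The size of a form-only count can be shown only under assumed rates.

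1. Patients with events off the form, if 20% to 60% of the miltefosine arm have vomiting or diarrhoea judged probable: 0.20 × 60 = 12 and 0.60 × 60 = 36. The exception removes none in the antimony arm.
2. Let q be the rate of any other adverse event (same in both arms), and g_M and g_A the rates of vomiting or diarrhoea under miltefosine and antimony. Take them as independent of q, with all such events under miltefosine judged probable. With all sources, the any-event rate is 1 − (1 − q)(1 − g). From the form alone, the miltefosine rate falls to q and the antimony rate is unchanged. The shift is therefore −(1 − q) × g_M.
3. For q of 20% to 40% and g_M of 20% to 60%, the smallest shift is 0.60 × 0.20 = 12 points and the largest is 0.80 × 0.60 = 48 points.
4. Example with q = 20%, g_M = 40%, g_A = 20%. All sources: 1 − 0.80 × 0.60 = 52% against 1 − 0.80 × 0.80 = 36%, a difference of +16 points. Form alone: 20% against 36%, a difference of −16 points.
5. If module and form entries are combined, the shift in incidence is zero.

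**The case against.** A reader might infer that the safety comparison is biased towards miltefosine and that its commonest toxicity leaves the count. The documents do not support this. The events are kept, with a CTCAE grade, and a graded event supplies both incidence and severity. No text says the endpoint is taken from the adverse-event form alone, and the choice of sources may properly be left to an analysis plan that is not shown. Nor does the protocol give frequencies: section 5.2 lists gastrointestinal, liver and renal effects together without ranking them. All of this stands.

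The two rules can also be read as compatible. The general rule asks for the relevant page of the report form, and this translated text elsewhere seems to use medical records for form pages, so the modules may simply be other pages of the form. That softens the contradiction. It does not remove the dependence on arm and causality.

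The protocol does not say that the modules record intensity exclusively, and the modules are not shown. This is a fair caution: dates and seriousness are unlisted, which is not proof that they are absent. As intensity is the one item specified, however, the protocol gives no assurance that the rest will be collected.

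A reader might also see a second bias in the ECGs that the section 4.6 flowchart assigns to control patients only. That does not carry over. Under section 3.4, an ECG abnormality goes on the adverse-event form only if it was serious, led to discontinuation or required treatment. Section 5.2 names arrhythmias as an antimonial toxicity, which gives a safety reason for the ECGs. Leaving such findings out of the comparison would discard real antimony toxicity.

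**Conclusion.** The point holds as a fault in how the data are collected. Recording of miltefosine's known reactions depends on the arm and on an unblinded causality judgement, for events that belong to a named secondary endpoint. An analysis plan can repair this only in part: combining the sources recovers incidence and grade, but not dates or seriousness if the modules omit them.

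A form-only count would understate miltefosine events by an unknown amount. The figures of 12 to 36 of 60 patients and 12 to 48 percentage points rest wholly on assumed rates and, for the percentage points, on independence and on every miltefosine case being judged probable. They show that the sign of the difference could reverse, not that it will. The primary endpoint, final cure at 6 months, is not affected.

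**What to change.** Reconcile the two rules in section 3.4. Record vomiting and diarrhoea in the same way in both arms whatever the causality. This can be done on the adverse-event form, or in a module used in both arms that holds dates, grade, seriousness and causality. State that all such events count in the adverse-event endpoint. The separate modules need not be abolished.

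The cost is protocol and report-form wording and a little more data entry, with no new procedure. The reported miltefosine adverse-event rate may be higher as a result. The change is best made before data collection starts, since items not collected cannot be reliably restored later.

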#### *Safety parameters*

The following safety assessments should be performed routinely with every patient. For more details on the frequency and extent, see Flowchart (item 4.5).

#### *Medical laboratory tests*

Clinical laboratory tests comprise the following parameters:

|              |                                                              |
|--------------|--------------------------------------------------------------|
| Hematology   | leukocytes, hemoglobin, platelets (thrombocytes)             |
| Electrolytes | sodium, potassium                                            |
| Substrates   | Albumin levels, total bilirubin, creatinine, urea            |
| Enzymes      | SGOT / AST SGPT / ALT, alkaline phosphatase                  |
| Urinalysis   | record of blood and protein only                             |
| Pregnancy    | β-HCG, presence or absence, in women who may become pregnant |

Additional tests will be performed when clinically indicated.

#### *Criteria and definitions*

Normal levels of local laboratory of the participating institution.

The investigator will classify each laboratory value outside the normal range:

1. Abnormal but of secondary importance
2. Abnormal and important relevance (seriously, led to discontinuation, requested a therapeutic measure) should be made to their record in the clinical record
3. Invalid value, must be specified the reason for this trial.

#### *Vital parameters*

Vital parameters to be recorded include systolic blood pressure, diastolic blood pressure, pulse, body weight and body temperature.

The investigator should comment on the respective section of medical records, the changes compared to baseline that are considered clinically relevant.

## **4. STUDY PROCEDURES**

### **4.1 Pre-study evaluation / selection**

Before the first administration of study medication, the investigator will inform the patient verbally and in writing about the potential benefits and any risks associated with their participation in this study and obtain a consent in writing.

The assessment team to verify compliance with the criteria for inclusion / exclusion include:

**Medical history:** General medical history (demographic data, sensitivity to medications and allergies, medical history and surgical significance), concomitant medication, history of leishmaniasis, previous treatments

**Physical examination:** Will be recorded: blood pressure, pulse, weight, height, temperature.

**Medical laboratory tests \*** CBC (no differential), platelets, stool examination  
HIV serology by ELISA or rapid test  
Biochemistry (Na+, K+, urea, creatinine, ALT, AST, LDH, alkaline phosphatase)  
Urinalysis (record of blood and protein only)  
Pregnancy test:  $\beta$ -HCG serum  
Hepatitis C antibodies, HBsAg, anti HBc

\*) All laboratory studies conducted in laboratory validated and reviewed. Abnormal values (values outside the normal laboratory values - 3 benchmarks) will be specifically addressed in patient records.

A second evaluation (at baseline) to verify adherence to the criteria for inclusion / exclusion will be necessary if the time between the assessment team and the first administration of study medication more than two weeks. Include the variables as above for the assessment of selection. In a female patient that requires a waiting period for repayment of a pregnancy test, to repeat the screening tests is unnecessary in the absence of clinical deterioration.

### **4.2 Assessments during the study**

#### **Safety assessments:**

|                         |              |
|-------------------------|--------------|
| Vital parameters        | 7, 14, 21    |
| Adverse Events          | continuously |
| Laboratory              |              |
| - CBC                   | 7, 14, 21    |
| - Clinical Biochemistry | 7, 14, 21    |

### **4.3 Assessments at the end of treatment**

The end of treatment will be the 28th day in the case of regular treatment. In case of premature discontinuation, all assessments listed below will be executed whenever the treatment is discontinued.

#### *Variable security:*

Vital parameters

Adverse Events

Laboratory tests (CBC, clinical biochemistry, urine)

Pregnancy test in women who may become pregnant

*Overall assessment:* Reason for discontinuation, overall assessment of tolerability  
A variation of the assessments plus / minus 2 days is acceptable. If these variations are not met, the reason should be documented in the appropriate page of medical records.

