#### 3.2.2 Exclusion criteria

*Safety concerns:*

- Thrombocyte count  $<30 \times 10^9/l$
- Leukocyte count  $<1 \times 10^9/l$
- Hemoglobin  $<5 \text{ g}/100 \text{ ml}$
- ASAT, ALAT, AP  $\geq 3$  times upper limit of normal range
- Bilirubin  $\geq 2$  times upper limit of normal range
- Serum creatinine or BUN  $\geq 1.5$  times upper limit of normal range
- Evidence of serious underlying disease (cardiac, renal, hepatic or pulmonary)
- Immunodeficiency or antibody to HIV
- Severe protein and/or caloric malnutrition (Kwashiorkor, Marasmus).
- Any non-compensated or uncontrolled condition, such as active tuberculosis, malignant disease, severe malaria, HIV, or other major infectious diseases
- Lactation, pregnancy (to be determined by adequate test) or inadequate contraception in females of childbearing potential for treatment period plus 2 months

*Lack of suitability for the trial:*

- Any history of prior anti-leishmania therapy
- Any condition which compromises ability to comply with the study procedures
- Concomitant serious infection other than cutaneous

*Administrative reasons:*

- Lack of ability or willingness to give informed consent (patient and/or parent / legal representative)
- Anticipated non-availability for study visits/procedures

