#### 4.5 Assessments 6 months after the end of the treatment

**Efficacy variables:** Lesion size / epithelization grade / size of the infiltration in the lesion  
Photograph of each lesion  
Leishmania parasitology

**Variable security:** Vital parameters  
Laboratory parameters (CBC, clinical biochemistry)

**Overall Assessment** Results of the study and response to therapy

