| Pregnancy test (women of childbearing age)               |       | x c) |       |       | X      |        |                         |                                  |                                  |                                   |                                   |                                   |
| HIV Testing                                              |       | x               |       |       |        |        |                         |                                  |                                  |                                   |                                   |                                   |
| Effectiveness                                            |       |                 |       |       |        |        |                         |                                  |                                  |                                   |                                   |                                   |
| - Parasitology                                           |       | x               |       |       |        |        | x                       | x                                | x                                | x                                 | x                                 | x                                 |
| - Size / degree of epithelization / area of infiltration |       | x               |       | x     | x      | x      | x                       | x                                | x                                | x                                 | x                                 | x                                 |
| - Photo d)                                    |       | x               |       |       | x      |        | x                       | x                                | x                                | x                                 |                                   | x                                 |
| Laboratory:                                              |       |                 |       |       |        |        |                         |                                  |                                  |                                   |                                   |                                   |

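### Four safety instructions are wrong or contradictory as written: the liver-injury and drug-expiry sentences are reversed, and text and flowchart disagree on the end-of-treatment pregnancy test and the post-treatment laboratory visit

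*Protocol*

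**What the plan says.** **Liver injury (3.2.3, lack of tolerance).** For grade 3 transaminase elevation the investigator may go on treating until there is no sign of liver injury, with jaundice as the example. The next sentence requires an immediate stop for grade 4 enzyme elevation or clinical signs of liver damage.

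**Expiry (3.3.1).** The sentence on the re-examination or expiration date says that the drug is to be used after that date. The following sentences have the monitor act in good time if drug is needed beyond it, with written notice of any extension.

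**Pregnancy test.** Section 4.3 lists "Pregnancy test in women who may become pregnant" at the end of treatment and adds: "In case of premature discontinuation, all assessments listed below will be executed whenever the treatment is discontinued". The flowchart row "Pregnancy test (women of childbearing age" is marked at visit 1 and at visit 4 (Day 14). Visit 6, which is Day 28 or final therapy, is empty. Footnote b says of visit 6: "It should be evaluated fully when treatment is discontinued". Section 4.2, "Assessments during the study", lists no pregnancy test on Day 14.

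**Laboratory tests.** Section 4.5 lists "Laboratory parameters (CBC, clinical biochemistry") at 6 months. Section 4.4, which covers 2 weeks, 1 month and 2 months, lists efficacy variables only. The flowchart marks blood count, biochemistry and urine at visit 8 (1 month) and none of them at visit 11 (6 months).

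**The concern.** Sites act on these instructions directly. Taken literally, the first two tell staff to do the opposite of what is safe. The other two mean that the tests a patient receives depend on whether the site works from the text or from the chart. A site using the flowchart alone would omit the end-of-treatment pregnancy test and the 6-month bloods. A site using the text alone would omit the 1-month bloods. Section 5.2 reports a teratogenic potential in preclinical work and names the liver among the main sites of adverse effects, so these are relevant safeguards for this drug.

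**Working it through.** The protocol gives no figure to reproduce. The check sets the instructions side by side.

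**1. Liver sentence.** Treating *until* injury is absent presupposes that injury is present while treatment goes on. The next sentence demands a stop in exactly that state. Both cannot be followed. Replacing *until* with *only as long as* makes them agree.

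**2. Expiry sentence.** If use after the date were the rule, the following sentences on timely action and written notice would have no purpose. They make sense only if use after the date is barred unless it has been extended.

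**3. Pregnancy test.** The flowchart rows, read across the 11 visits, give this:

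| Situation | Last test, section 4.3 | Last test, flowchart |
|---|---|---|
| Completes 28 days | Day 28 | Day 14 |
| Stops before Day 14 | At discontinuation | Before therapy |

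For a completer the sources differ by 28 − 14 = 14 days. For a woman who stops before Day 14, the flowchart as printed gives no test once treatment has begun.

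**4. Blood count and biochemistry.**

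| Source | Time points | Count |
|---|---|---|
| Sections 4.1, 4.2, 4.3, 4.5 | Screening; Days 7, 14, 21, 28; 6 months | 6 |
| Flowchart | Screening; Days 7, 14, 21, 28; 1 month | 6 |
| Shared | Screening; Days 7, 14, 21, 28 | 5 |
| Either source | All of these | 7 |

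A shifted column is an unlikely explanation. The blood count, biochemistry and urine rows all point to visit 8. The Day 7, 14 and 21 marks match section 4.2. The photograph row is marked at every time named in section 3.4 (before, Day 14, Day 28, and 1, 2 and 6 months).

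**5. Cost of keeping both laboratory visits.** With the 90 patients of section 3.2, one source alone means at most 90 × 6 = 540 draws. Both mean at most 90 × 7 = 630. The difference is at most 90, of which 30 are in Group 1 (ages 2 to 12). This prices the remedy; it does not measure harm from the error.

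**The case against.** The strongest reply is that the document largely corrects itself. The sentences around both reversed instructions show the intent, and the protocol reads throughout as a rough translation. That stands as an account of how the errors arose and as a reason to rate them low. The two sentences are still wrong as instructions.

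On the pregnancy test, the Day 14 mark is a single capital letter and may have moved when the table was read from PDF. If it belongs at visit 6, the disagreement disappears. An intact row of cells does not settle this, because a misplaced mark leaves the cell count unchanged. In any case section 4.3 already requires the test, and footnote b asks for a full evaluation at that visit. This objection largely stands. What remains is a chart to be checked and, if confirmed, completed.

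On the laboratory visits, neither source forbids the other's draw, so a site following both would miss nothing. Section 3.4 also sends the reader to the flowchart for frequency and extent. But it numbers that flowchart 4.5, which is the 6-month section in conflict with it, so it is not a usable rule of precedence.

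A reader might infer that women are left unprotected. The documents do not support that. Section 3.2.2 excludes pregnancy and "inadequate contraception in females of childbearing potential for treatment period plus 2 months". Footnote c covers testing before treatment, and for women screened later in the cycle it adds: "After the waiting period should be performed a confirmatory test of pregnancy, before randomization". In a patient who completes the course, a Day 28 test can detect a pregnancy but cannot undo exposure already received.

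A reader might also infer bias in the adverse-event endpoint. Section 3.4 calls for documenting events that occur during study treatment, and both disputed draws come later, so that inference is not supported either.

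**Conclusion.** The point holds as a minor one, confined to patient safety. Two sentences are reversed as written, and two schedule items differ between text and flowchart. The primary endpoint, the secondary endpoints and the analysis are unaffected.

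The two wording errors are certain on the page. The laboratory conflict is well supported by the agreement of the surrounding rows. The pregnancy-test conflict depends on the Day 14 mark being where it appears; if it is an extraction artefact, the other three items still stand. The document does not give the number of women concerned, so no count is offered.

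There are smaller mismatches nearby: vital-sign visits, a 4-month visit without a text section, total bilirubin missing from the screening list in 4.1, and two wrong section numbers. A reader might take these as further evidence of unsafe conduct. They are editorial or resolved elsewhere (the laboratory panel in 3.4 includes bilirubin) and form no part of this conclusion.

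**What to change.** One amendment is enough.

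- **3.2.3:** in the grade 3 transaminase sentence, replace *until* with *only as long as*, so that treatment may continue only while no sign of liver injury, such as jaundice, is seen.
- **3.3.1:** insert *not* after *must* in the expiry sentence.
- **4.6, pregnancy row:** mark visit 6. Check the Day 14 mark against the source table. If it is genuine, list that test in 4.2; otherwise remove it.
- **4.4, 4.5 and 4.6, laboratory:** mark blood count and biochemistry at both 1 and 6 months in the flowchart, and list the 1-month tests in 4.4, saying whether urine is included. Alternatively, delete one of the two visits explicitly in both places.

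The wording changes cost nothing, and the visit 6 mark adds no test beyond what 4.3 already requires. Keeping both laboratory visits costs at most one extra draw per patient compared with following one source alone; deleting one visit avoids that.
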